## Abstract

**Background:**

Problem drinkers have poor inhibitory control (disinhibition). Previous studies have demonstrated that various forms of ‘inhibition training’ can reduce alcohol consumption in the laboratory and at short-term follow-up, but their longer-term efficacy and mechanisms of action are unknown. In this phase 2 randomised controlled trial we will contrast the effects of three forms of inhibition training and a control intervention, delivered via the Internet in multiple sessions over four weeks, on alcohol consumption in heavy drinkers.

**Methods/design:**

Heavy drinkers who are interested in reducing their alcohol consumption will receive a brief intervention and will monitor their own alcohol intake for one week before being randomised to one of four treatment groups: 1. General inhibition training; 2. Cue-Specific inhibition training; 3. Alcohol No-Go training; or 4. Control. They will complete up to 14 sessions of training via the Internet over a four-week period, and will be followed-up for a further six weeks after the end of the training period. Primary outcome measures are reductions in alcohol consumption and heavy drinking days. The number of abstinent days is a secondary outcome measure. We will also investigate changes in inhibitory control and automatic alcohol affective associations in response to training.

**Discussion:**

This study will establish if web-based inhibition training can help problem drinkers to reduce their alcohol intake, and it will identify which form(s) of inhibition training are most effective.

**Trial registation:**

Trial Registation number: ISRCTN55671858.

## Background

Disinhibition - the inability to suppress, delay or change a response that is no longer required or is inappropriate - is a core feature of both impulsivity and executive functioning [1, 2]. The construct can be measured using computerised tasks such as the Stop-Signal (SST [3]) and Go/No-Go tasks (GNGT [4]). In these tasks, participants must override a dominant motor response when faced with a ‘Stop’ or ‘No-Go’ cue, respectively. Disinhibition is associated with individual differences in drug and alcohol consumption [5, 6], it predicts hazardous drinking [7] and distinguishes alcoholics from healthy controls [8]. Disinhibition is not merely a consequence of problem drinking because it *precedes* changes in alcohol involvement: it predicts future drinking behaviour in adolescents [9], slow development of inhibitory processes during adolescence predicts problem drinking later in life [10] and disinhibition predicts the likelihood that heavy drinkers will transition to alcohol dependence [11].

Disinhibition is not a stable trait, but rather a transient state that fluctuates in response to environmental triggers. Alcohol-related cues provoke temporary increases in disinhibition in heavy drinkers [12, 13] and alcoholics [14, 15]. Other arousing cues, acute stress, and self-control depletion also lead to increased disinhibition, and it is hypothesised that these fluctuations in disinhibition increase the risk of drinking to excess [1, 16]. Encouragingly, inhibitory control can be improved with practice. One study [17] demonstrated that repeatedly practicing the SST led to improved inhibitory control, whereas in another [18] key parameters of the SST were changed such that it became more difficult over time. Both studies demonstrated progressive improvements in inhibitory control that were accompanied by changes in markers of brain activity that are associated with inhibitory control (see also [19, 20]).

Inhibitory control is malleable and it has a causal influence on problem drinking, which makes it a viable target for clinical interventions [16, 21]. We demonstrated that priming restrained behaviour during the SST led to improvements in inhibitory control and reductions in alcohol consumption in the laboratory [22, 23]; comparable effects have been reported on food intake [24, 25] and gambling [26, 27]. Another laboratory study demonstrated that if participants completed a modified SST in which they learned to inhibit behaviour only in the presence of alcohol-related cues, this led to an improvement in inhibitory control that was specific to alcohol cues, and was accompanied by a reduction in alcohol consumption in the laboratory [28]. Thus, training of both *cue*-*specific* and *general* inhibitory control may prompt reductions in alcohol consumption. Other studies demonstrated that pairing inhibition with alcohol-related cues during a modified GNGT did not directly improve disinhibition (measured with the SST), but it did change affective associations with alcohol and led to reduced alcohol consumption after a one week follow-up [29, 30]; see also [31]).

These recent laboratory studies suggest that training of inhibitory control using modified versions of the SST and GNGT can lead to reductions in alcohol consumption, although the underlying mechanisms may differ across tasks. We suggest that this is because of distinct inhibitory and associative learning processes that are engaged during the GNGT and the SST. The GNGT measures automatic or bottom-up inhibition because the decision to inhibit is made as soon as the No-Go cue is detected, and this inhibition can be consistently paired with a particular stimulus such as an alcohol-related cue [32, 33]. On the other hand, the SST measures controlled or top-down inhibition because the stop signal is not presented until after a motor response has been initiated, which makes it more difficult to pair inhibition with a particular stimulus such as an alcohol cue. Given these differences between tasks, training inhibitory control using the SST may not generalise to improved performance on the GNGT, and vice versa [29, 33]. Furthermore, automatic inhibition leads to devaluation of No-Go cues [34], whereas there is no evidence that controlled inhibition alters the valuation of Stop signals.

Laboratory studies involving a single session of inhibition training are an important first step in establishing proof of concept that such training could be a viable clinical intervention. However, research into other types of cognitive training for alcohol problems suggests that multiple sessions of training are needed to produce longer-lasting reductions in alcohol consumption and cognition that generalise outside of the training context [35–38]. Related to this, a recent study on inhibition training for weight loss demonstrated that repeated food-related GNGT training via the internet led to significant weight loss that was maintained over four weeks [39]. Other interventions for problem drinking are also effective if delivered online in multiple sessions [40]. Overall, it appears that i) interventions targeting behaviour change are more effective if repeated in multiple sessions and ii) delivery of such interventions via the Internet can be efficient, cost-effective and efficacious [41, 42].

### Aims and hypotheses

The aim of this study is to examine the efficacy of repeated inhibition training as an intervention to reduce alcohol consumption in heavy drinkers recruited from the local community. We will recruit individuals who consume alcohol in excess of UK government guidelines for safe drinking, and who are motivated to cut down [43]. Most heavy drinkers never seek treatment [44, 45], and without treatment they are likely to transition into more harmful patterns of drinking [46]. Heavy drinkers who are not severely alcohol dependent are also less likely to engage with abstinence based treatments [47]. However, a significant proportion of regular drinkers express desires to reduce their alcohol consumption [48]. Therefore a reduction in alcohol consumption is a viable goal for interventions for this population [49, 50].

In order to ensure that they are motivated to reduce their drinking, all participants will complete a brief intervention (‘Down Your Drink’ (DYD) [51]) followed by one week of monitoring of their alcohol consumption before they begin inhibition training. This brief intervention and self-monitoring period are also included in the study for pragmatic purposes. Many heavy drinkers will reduce their alcohol consumption after a brief intervention and/or a period of self-monitoring, and failure to control for these ‘non-specific’ effects can obscure effects of active treatments [52, 53].

Participants will be randomly allocated to one of four groups: 1. General inhibition training; 2. Cue-Specific inhibition training; 3. Alcohol No-Go training; or 4. Control. All participants will complete an internet intervention 14 times over a four-week period (every other day, on average). Their alcohol consumption will be monitored throughout the training period. We predict reductions in alcohol consumption during the training period in the first three groups compared to the control group. This will be the first study to directly compare these three types of inhibition training, so we have no *a priori* hypotheses about which will produce the largest reduction in alcohol consumption.

We will monitor participants’ alcohol consumption at two, four and six-weeks after the end of the intervention (follow-up). We predict that any group differences in alcohol consumption that are seen at the end of the training period will be maintained throughout the follow-up period.

We will also investigate psychological changes that occur as a result of inhibition training. We predict that Alcohol No-Go training will cause changes in automatic alcohol affective associations [29, 34], whereas General inhibition training will lead to non-specific improvements in inhibitory control [18], and Cue-Specific inhibition training will lead to improvements in inhibitory control that are specific to alcohol cues [28].

## Methods/design

### Participants

Participants will be recruited from the local community through advertisements in the local media and via employers and local community organisations. Eligible participants will i) be aged between 25–65, ii) drink over UK government guidelines for safe drinking ([43]: more than 14 UK units for females and 21 UK units for males, where 1 UK unit = 8 grams of alcohol)) iii), be interested in trying to reduce their alcohol consumption.

Exclusion criteria include i) any history of treatment for an alcohol use disorder, and ii) a current or previous diagnosis of substance use disorder (including alcohol use disorder), and/or attention deficit disorder, because these conditions are associated with poor inhibitory control [54]. Participants will be required to have access to the Internet from a desktop or laptop computer, and an email address. The study received ethical approval from the Institute for Psychology, Health and Society Research Ethics Committee.

#### Sample size and randomisation

We used G*Power 3.1.5 [55] to calculate the required sample size for power of 0.80 to detect any main effect or interaction (numerator df = 3) at an alpha level of 0.05 (see Table 1). We based this calculation on a recent meta-analysis concerning e-help interventions for problem drinkers [41] which demonstrated a medium effect size (f = 0.25). As seen in Table 1 we require a total sample size of 179 to detect an effect.

## Materials

### Questionnaires

During their initial visit to the laboratory, participants will complete the two-week timeline follow-back alcohol consumption diary (TLFB [59]), the Alcohol Use Disorders Identification Test (AUDIT [60]), the Barratt Impulsivity Scales version 11 (BIS [61]) and the Temptation and Restraint Inventory (TRI [62]).

#### Pictorial stimuli

Ten alcohol-related and 10 matched neutral pictures, a subset of those used in our previous inhibition training study [28], will be used in the training and control tasks. Alcohol-related pictures depict alcoholic drinks that are common in the UK, and individuals holding or consuming those drinks, whereas neutral images depict pictures of stationery and office furniture. Picture pairs are matched on perceptual characteristics such as complexity and brightness. Smaller subsets of these picture pairs are used in the Cue-Specific SST and the Alcohol Valence Implicit Association Task (see below).

#### Computer tasks

All tasks will be programmed and administered using Inquisit 3.0 [63]. Baseline and follow-up tasks will be completed on a laptop or desktop PC in a lab at the University of Liverpool, whereas online tasks will be hosted by Inquisit 4.0 web edition [64].

#### Tasks administered in the laboratory

*Standard SST*
[65]: We will use a standard version of the task that incorporates arbitrary visual stimuli (the letters X and O) along with the tracking procedure to set the stop signal delay (SSD). The initial delay will be 250 ms and will increase by 50 ms after every successful inhibition and decrease by 50 ms after every failure to inhibit. The critical variable is Stop Signal Reaction Time (SSRT), the estimate of stopping latency.

*Cue*-*Specific SST*
[66]: Participants will categorise images of alcoholic drinks based on their orientation (portrait or landscape). The same dynamic algorithm and number of trials as the standard task will be used. A measure of alcohol cue-specific SSRT will be computed from this task. Eight alcohol pictures will be used in the task.

*Alcohol Valence Implicit Association Task* (AVIAT) [29]: Participants will be required to categorise stimuli into two target categories (Alcohol or Neutral images) and two affective attribute categories (Positive and Negative words). The *D* measure ([67] will be calculated as an indicator of the strength of alcohol-positive associations. Six picture pairs will be used in the task.

#### Training tasks administered via internet

Both Cue-Specific and General SST training will be implemented using modified versions of the SST. The Alcohol No-Go training takes the form of a modified GNGT. The Control intervention is similar to the Cue-Specific SST with the crucial difference that it contains no Stop signals. Each training session will take approximately seven minutes to complete.

*Cue*-*Specific inhibition training* (*see Figure *1): Participants will be required to rapidly categorise pictures as alcohol-related or stationery-related, by pressing the ‘X’ or the ‘M’ key on their keyboard. There will be 200 trials separated by a short break after half the trials. On 75% of all trials in each block this categorisation will not be interrupted; these are Go trials. On the remaining 25% of trials, two red lines (the Stop Signal) will be superimposed over the picture after a fixed SSD. Participants will be instructed to inhibit their response to the picture whenever they see the Stop signal, and wait for the next trial. The Stop Signal will appear on 50% of alcohol trials, but never on neutral trials. Therefore, participants should learn the contingency that presentation of an alcohol related picture may signal inhibition, but this is not always the case. This is important because cue-specific inhibition training requires participants to learn the contingency between alcohol and inhibition, but we cannot present the stop-signal on 100% of alcohol trials (50% of total trials), because this would encourage participants to adopt a waiting strategy, particularly in the presence of alcohol cues [68].

**Figure 1 Fig1:**
[figure not shown]
**Schematic representation of trials in Cue-Specific inhibition training.**

Training will be adaptive based on performance over sessions. It will become progressively more difficult as performance improves, thereby leading to improved cue-specific inhibition over time. The initial fixed SSD will be 250 ms and in the first session each stop trial will implement this delay. Once participants are able to inhibit to at least 50% of stop trials during a block at this delay, the SSD in the following block will increase by 10 ms in the next session, making inhibition more difficult. Therefore, the maximum (most difficult) SSD at the end of training will be 380 ms [250 ms + (10 ms X 13 sessions with potential increments)].

*General Inhibition training* (*see Figure*2): This group will complete a modified version of the Stop-Signal task using arbitrary stimuli (the letters X and O). In this version the Stop Signal will be superimposed over 50% of the X stimuli and none of the O stimuli. There will be 200 trials in total, 25% of which are Stop Signal trials. As with Cue-Specific inhibition training, the initial SSD will be set at 250 ms and if participants successfully inhibit on at least 50% of Stop trials within a block the SSD will increase by 10 ms in the next block.

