#### Supplementary analyses

If there are group differences in outcome measures at the end of training, we will analyse follow-up data using a separate mixed-design ANOVA with a between-subject factor of treatment condition, and a within-subject factor of time (3: two-week, four-week and six-week follow-up).

The effects of treatment condition on general inhibition, cue-specific inhibition and automatic alcohol-affective associations will be analysed using mixed-design ANOVA with a between-subject factor of treatment condition, and a within-subject factor of time (2: before training vs. after training).

The responses from the subgroup of participants who return to the laboratory for an interview about their experiences of taking part in the trial will be analysed using thematic analyses to identify themes related to treatment efficacy, acceptability and barriers to use (see [71]).

Any further exploratory analyses will be labelled as exploratory in the final publication.

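### Gains on the laboratory stop-signal tests may be learning of the trained stimuli, and the stated ANOVAs do not test whether improvement is specific to alcohol cues

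*Protocol article*

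**What the plan says.** **Predictions.** In Aims and hypotheses the article predicts that "General inhibition training will lead to non-specific improvements in inhibitory control". It predicts that the improvement after Cue-Specific training will be confined to alcohol cues.

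**General training** (Training tasks administered via internet): "This group will complete a modified version of the Stop-Signal task using arbitrary stimuli (the letters X and O"). The contingency is that "the Stop Signal will be superimposed over 50% of the X stimuli and none of the O stimuli".

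**Laboratory standard SST** (Tasks administered in the laboratory): "We will use a standard version of the task that incorporates arbitrary visual stimuli (the letters X and O").

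**Pictures** (Pictorial stimuli): ten alcohol and ten neutral pictures "will be used in the training and control tasks". For the laboratory tasks, "Smaller subsets of these picture pairs are used in the Cue-Specific SST and the Alcohol Valence Implicit Association Task". The cue-specific SST uses eight alcohol pictures, and no stop-signal reaction time (SSRT) for neutral pictures is described.

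**Analysis** (Supplementary analyses): general inhibition, cue-specific inhibition and affective associations are analysed by mixed ANOVA with treatment condition between subjects and "a within-subject factor of time (2: before training vs. after training"). No task or cue factor is named.

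**Who is tested** (Procedure): every continuing participant takes both SSTs before training and again after it.

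**The concern.** General training pairs stopping with one letter of a pair, in the same way as Cue-Specific training pairs stopping with alcohol pictures. The article relies on that schedule to teach an alcohol–stop link, so it could equally teach an X–stop link. The General arm is then tested on the same two letters, which no other arm has had as stimuli. An improvement on the standard SST in that arm has two explanations, better inhibition in general or learning tied to those letters, and the test cannot separate them.

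The laboratory cue-specific SST has a milder form of the same problem, because its pictures come from the trained set.

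The second weakness lies in the analysis. A claim that improvement is specific to alcohol cues is a claim about the difference between changes on two tests. Analysing each test by condition and time alone never estimates that difference. Finding one result significant and the other not does not show that the two differ. What is at stake is the interpretation of the mechanism results, which the Discussion presents as a theoretical contribution of the trial.

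**Working it through.** **1. The plan's own figure.** With f = 0.25, four groups, numerator df 3 and α = 0.05, λ = 0.25² × 179 = 11.1875, the critical F is 2.656 on 175 denominator df, and power is 0.8015. The smallest N reaching 0.80 is 179, as in Table 1. 179 / 0.67 = 267.2, rounded up to 268, also agrees. These figures neither support nor weaken the point; they only set the N used in step 4.

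**2. What each arm has practised before each laboratory test.**

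| Arm | Training stimuli | Inhibition in training | Standard SST (X, O) | Cue-specific SST (alcohol pictures) |
|---|---|---|---|---|
| General | X, O | stop on 50% of X, never on O | trained stimuli | untrained stimuli |
| Cue-Specific | pictures | stop on 50% of alcohol, never on neutral | untrained | trained, with stopping |
| Alcohol No-Go | pictures with P or R | withhold on all alcohol trials | untrained | trained, with withholding |
| Control | pictures | never | untrained | seen, never with stopping |

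(X is also a response key in the Cue-Specific and Control tasks, but not a stimulus there.)

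**3. Amount of practice at full compliance.**
- General: 14 sessions × 200 trials = 2,800 trials. Stops: 25% × 200 = 50 per session; 50 × 14 = 700, all on X.
- Cue-Specific: the 50 stops per session are half of the alcohol trials, so there are 100 alcohol trials per session. If the ten pictures are used equally, 100 × 14 / 10 = 140 showings per picture, of which 700 / 10 = 70 carry a stop signal.
- Control: also categorises alcohol and neutral pictures in 200 trials per session. The split is not stated; if even, it too gives 140 showings per alcohol picture, with no stops.

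Picture exposure is therefore roughly balanced between Cue-Specific and Control, but pairing of particular pictures with stopping is not. These counts describe opportunity to learn; they do not estimate a bias in SSRT.

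**4. Inferring specificity from two analyses.** Let A be the change on the alcohol-picture SST and L the change on the letter SST. Specificity concerns A − L. The stated ANOVAs test A and L, each across four arms.

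Change scores were simulated (10,000 runs per setting) with one arm differing. The arm pattern (1, 0, 0, 0) has SD √3/4 = 0.433, so f = 0.25 is a shift of 0.25 / 0.433 = 0.58 SD. The correlation r between A and L is not in the article and was varied from 0 to 0.7. N = 180 approximates the sample left after excluding 33% (268 × 0.67 = 179.6).

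*Equal true improvement on both tasks* (no specificity):

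| r | Alcohol significant, standard not: N = 180 | N = 268 |
|---|---|---|
| 0 | 15.4% | 5.3% |
| 0.3 | 13.6% | 4.9% |
| 0.5 | 11.9% | 3.8% |
| 0.7 | 9.1% | 3.6% |

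The condition × time × task test errs in about 5% in every setting.

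*True improvement on the alcohol SST only:* the effect size for the three-way test is 0.25 / √(2(1 − r)).

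| r | f for A − L | Power, N = 180 | Power, N = 268 |
|---|---|---|---|
| 0 | 0.177 | 0.480 | 0.669 |
| 0.3 | 0.211 | 0.645 | 0.833 |
| 0.5 | 0.250 | 0.804 | 0.941 |
| 0.7 | 0.323 | 0.962 | 0.997 |

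These figures are for the four-arm test with 3 df, not for the single contrast of Cue-Specific with Control.

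**The case against.** A reader might infer that the predicted improvements cannot be shown at all. The documents do not support that. Both SSTs are taken by everyone, so the alcohol-picture SST is an untrained-stimulus test for the General arm. General versus Control on that measure can support non-specific improvement within the stated ANOVA, and an X–stop link could not explain it. The letter SST serves likewise as a transfer test for the Cue-Specific arm. This objection stands, although the article does not name either comparison as the test of its predictions.

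A reader might also infer that repeated viewing of the test pictures favours the Cue-Specific arm over Control. It does not, because Control sees the same pictures. Pairing alcohol with stopping is the intended active ingredient. The laboratory task also asks for an orientation judgement with a tracked delay, whereas training asks for alcohol versus stationery with a delay fixed within a block. What remains is that learning about particular pictures is not distinguished from learning about alcohol cues at large.

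Reuse of pictures in the implicit association task is no evidence about inhibitory control: that task measures affective associations, and the prediction about it concerns Alcohol No-Go training.

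The direction and size of any bias on the standard SST are not established. The article does not say how stop signals are divided between X and O in the laboratory version.

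Finally, a condensed article may leave model detail to an analysis plan, and for these measures it does not use the word separate. But it does state the factors, and task is not among them, so one ANOVA per measure is the natural reading.

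**Conclusion.** The point holds in a limited form. On the standard SST, a gain of General over Control is ambiguous, because only that arm has practised the test letters (up to 2,800 trials, 700 of them stops, all on X). On the cue-specific SST, exposure is balanced against Control but item–stop learning is not, and generalisation to untrained alcohol pictures is not examined. The prediction of alcohol-specific improvement has no test in the stated analysis.

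The false suggestion of specificity is modest in size: about 9–15% at N = 180 and 4–5% at N = 268 when improvement is in fact equal. This assumes one affected arm, f = 0.25 on change scores and correlations of 0 to 0.7. At full sample size the rate is near or below the nominal 5%; the main fault is that the relevant difference is never estimated.

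Only the supplementary mechanism analyses are affected. The co-primary drinking outcomes, their analysis and the sample size are untouched.

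**What to change.** 1. **Standard SST.** Use letters or shapes other than X and O in the laboratory version at both visits. Failing that, name General versus Control on the alcohol-picture SST as the test of non-specific improvement.
2. **Analysis.** Pre-specify a joint SSRT analysis with task as a within-subject factor, and test specificity by condition × time × task, with Cue-Specific versus Control as the contrast. State that this compares alcohol pictures with letters and so does not by itself separate an alcohol effect from a picture effect, since no neutral-picture SSRT is described.
3. **Pictures.** If untrained alcohol pictures are available, use them in the laboratory cue-specific SST. The article says the training pictures are a subset of an earlier set but does not give that set's size, so availability needs checking.

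**Cost.** New stimulus lists, to be in place before the first baseline test, and one further model term on data already planned. No extra participants or visits are needed. The downside is that purely item-specific learning would no longer be detected.
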